### Statistical analyses

1.6

Due to the nesting of participants within family units, all analyses are conducted within a multilevel modelling framework, accounting for the interdependence in the data (children nested within parent). Attrition bias analyses will be conducted, comparing participants who only completed T1 to those who remained in the study after T1 (i.e. completed T2 and/or T3 assessment), using multilevel logistic regression, with drop-out as the outcome and baseline sociodemographic and psychological variables as predictors.

To examine the effectiveness of the intervention, multilevel regressions will be conducted to examine group differences on the primary outcomes: SDQ-Emotional (H1), SDQ-Total (H2), and SDQ-Impact (H3) at T3. These analyses will be based on the intention-to-treat principle (Gupta, 2011). Multiple imputations using chained equations as implemented in the R package mice will be applied to handle missing data. The regression models will be specified to allow for a random intercept, as well as for interdependence due to nesting of children within parent participants, using a generalized equating equation. Thus, in these analyses, participant responses are the unit of analysis. Group membership (i.e., SES NXT group (1) vs. control group (0)) will be entered as a categorical predictor; we will also include potential covariates, including participants' gender and age, participants' baseline score on the outcome, and parental educational level, income, and depression/anxiety symptoms. Following examination of the primary outcomes, the same analyses will be conducted with respect to the secondary outcomes. For all analyses, a *p*-value of less than 0.05 will be used as the threshold for statistical significance, since this value was used as the acceptable risk of type I error in our sample size estimation (see ‘Sample size’). Additional follow-up analyses will be executed to examine whether there is a differential change over time for the two groups, as reflected in a time-by-group interaction effect and, for the intervention group, to examine differences in the outcomes based on intervention age group and number of modules completed in the intervention.

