### Intervention description

1.4

SES NXT is a digital intervention for children and youth aged 3–17 years, who experience parental relationship dissolution. The intervention includes various elements such as text, videos, motion graphics, and voice-overs, and highly interactional content such as digital activities and exercises. SES NXT is designed to be adaptive to the youth's age. The intervention has four age categories correspond to the Danish daycare and school system, with 3–5-year-olds attending daycare and kindergarten, ages 6–8 years representing pre-school and start of primary education, ages 9–12 years representing primary education and start of lower secondary education, and ages 13–17 years representing lower secondary education and start of secondary education (e.g., high school). The format of the intervention was adapted to reflect the cognitive, social, emotional, and digital competencies of each of those age groups. Specifically, the intervention for children aged 3–5 consists of videos with speak that the parent and child can watch together and contain dialogue questions for the parent to initiate conversations with the child about the theme in question. Youth ages 6–8 are able to manage a digital tool on their own (with less parental guidance), but may not be able to read; therefore, the intervention consists of videos with speak and some short texts at a low reading level. For youth aged 9–12 and 13–17, the intervention consists of videos, texts, and interactive content, reflecting their greater reading level and digital competencies. However, the interventions for the two age groups differ with respect to their level of abstraction. Moreover, videos that contain other children (i.e., “peers”) present children in the same age range as the participants (e.g., 9–12-year-olds watch videos of other 9–12-year-olds).

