The intervention addresses key factors associated with adjustment to parental relationship dissolution, such as perceived support (Sorek, 2020), coping skills (O'Hara et al., 2019; Sandler et al., 2000), child-parent relations and communication (Gunter Castleton, 2020; Kunz, 2001; O'Hara et al., 2019; Wal et al., 2021), and the interpretation and meaning made of the relationship dissolution (e.g., loss, gain, change, healing) (Brand et al., 2017; Venta and Walker, 2021). Table 2 provides an overview of the modules included in the intervention for each age group. Each module comprises a theme identified in the literature as central to youths experiencing parental relationship dissolution (e.g., living in two homes, bonus families, and parental conflict). Most of the content in the intervention is covered across the age groups, though in age-appropriate ways. An example of this is the module(s) concerning emotions (i.e., “Feelings” for 3–5-year-olds and 6–8-year-olds and “Understand your feelings” for 9–12-year-olds and 13–17-year-olds), which covers the various emotions that one might experience in response to a parental relationship dissolution. Different emotions are described: sadness and longing, guilt, joy, fear and insecurity, anger. For the two older age groups, the text for sadness and longing is: “Sadness and longing are the best! Because it shows you that someone or something means a lot to you. In other words, it's a sign of love. But... isn't it bad to be sad? No, actually not. It can be tough and hard, but if you were never sad, it would actually be a little sad.” The texts are (often) the same for the 9–12- and 13–17-year-olds and they are introduced to an understanding of emotions as good, even though they can be difficult to experience.

**Table 2 t0010:** Intervention content overview, by age group in the intervention.

Theme	Age 3–5	Age 6–8	Age 9–12	Age 13–17
*Family Constellations*				
My Family	X			
The Bonus Family		X	X	X
*Practical Matters*				
Changeover Day	X			
Living in Two Places		X	X	X
Packing Your Bag		X	X	X
*Emotional Aspects of Parental Divorce*				
Missing Someone Means You Care	X			
Feelings	X	X		
Understand Your Feelings			X	X
When It has Just Happened		X	X	X
Tell Your Story			X	X
*Agency*				
Find an Important Adult		X	X	X
Learn To Say Yes and No		X	X	X
My Parents Are Not Getting Along		X	X	X
My Rights			X	X

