The intervention can be accessed at any time during the trial by logging into the intervention website from a mobile smartphone, tablet, or computer. Given that divorce is a heterogeneous process, and the experience of divorce is different for each individual, participants choose the modules that are most relevant to them. The modules can be completed in any order, as little or much as desired, and repeated as needed.

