### Measures

1.5

All questions are completed at baseline (T1), 4 weeks post-baseline (T2), and 12 weeks post-baseline (T3); parents complete questionnaires on behalf of their children aged 3–10, while youth aged 11–17 complete the questionnaires themselves. Table 1 provides an overview of the measurements in the study.

The Strength and Difficulty Questionnaire (SDQ; Goodman, 1997; Goodman et al., 1998) is used to measure emotional, behavioral, and social difficulties. The SDQ consists of a self-report version (from age 11) and proxy report version for parents, both including 25 items rated on a 3-point scale (i.e., 0 = “not true”, 1 = “somewhat true”, and 2 = “certainly true”). The items are divided into five 5-item subscales that generate a score for: 1) Emotional problems, 2) Conduct problems, 3) Hyperactivity/inattention, 4) Peer relationships problem, and 5) Prosocial behavior. Scores for each of the subscales can range from 0 to 10. A total SDQ difficulty score is calculated by summing up the difficulties across the four problem areas (not including prosocial behavior); scores range from 0 to 40, with higher scores indicating more mental well-being related difficulties. The extended version of the SDQ contains an impact scale that asks questions about child distress and interference of problems with home life, friendships, classroom learning, and leisure activities. The SDQ impact scale consists of 5 items, rated on a 4-point scale (i.e., 0 = “not at all”, 1 = “only a little”, 2 = “a medium amount”, and 3 = “a great deal”). The items are summed, and the resultant score can range from 0 to 10, with higher scores indicating greater impact of problems on daily life. The SDQ is a well-established and widely used measure that has shown good psychometric properties in a Danish sample (Arnfred et al., 2019; Niclasen et al., 2012). In this study, the SDQ-Emotional subscale, the SDQ-Total scale, and the SDQ-Impact scale serve as primary outcomes (Hypothesis 1, 2, and 3), while the remaining 4 subscale scores (conduct problems, hyperactivity/inattention, peer relationships problems, and prosocial behavior) are secondary outcomes (Hypothesis 4–7).

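### The age-group follow-up analysis uses the intervention arm only, so it cannot show whether the effect differs by age; the module-count analysis can only be descriptive

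*Protocol article*

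**What the plan says.** The Statistical analyses section (1.6) closes with additional follow-up analyses. One is between arms: differential change over time, "as reflected in a time-by-group interaction effect". The other is confined to one arm: "for the intervention group, to examine differences in the outcomes based on intervention age group and number of modules completed in the intervention". No interaction between arm and age group is named. The section sets p < 0.05 as the threshold for all analyses and does not label these as descriptive.

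Four other places bear on the point:

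- **Reporter.** The Measures section (1.5) states that "parents complete questionnaires on behalf of their children aged 3–10, while youth aged 11–17 complete the questionnaires themselves".
- **Age bands.** The Intervention description (1.4) sets four: 3–5, 6–8, 9–12 and 13–17. The third is described as "ages 9–12 years representing primary education and start of lower secondary education", so the change of reporter at age 11 falls inside it.
- **Module use.** The same section says that "participants choose the modules that are most relevant to them" and that "The modules can be completed in any order, as little or much as desired, and repeated as needed". Under Procedure (1.3), movie tickets in the intervention arm require three completed modules.
- **Age at sign-up.** Procedure states that each child's age is given on the sign-up form, so it is known in both arms.

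**The concern.** A comparison of treated children across age bands estimates how their scores differ by age. It does not estimate how the effect of SES NXT differs by age, because nothing in it shows what the scores would have been without the intervention. Three things other than the effect can separate the bands: different levels of symptoms at different ages, different natural change over 12 weeks, and the move from parent report to self-report. All three are present in the controls too, and a between-arm interaction would remove them.

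The module analysis has a different difficulty. Children or families who complete more modules may differ in motivation, need or parental support, and any of these can affect the outcome. The maximum count also rises with age band, so the raw count carries age with it.

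At stake is what these two analyses can support. The introduction motivates the programme by the need to cover several age groups, so readers will look to the age comparison for evidence on that question. As specified, it cannot give any.

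**Working it through.** The article gives no figure for these follow-up analyses, so there is none to reproduce. The check counts the available modules and then shows how far a within-arm contrast can move when the true effect is the same at every age.

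**Modules available (Table 2, X marks per column).** Ages 3–5: 4. Ages 6–8: 8. Ages 9–12: 10. Ages 13–17: 10. The three modules needed for a ticket are therefore 3/4 = 75%, 3/8 = 38%, 3/10 = 30% and 3/10 = 30% of what is on offer.

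**Stable gap between two bands, uniform effect.** Assumed, because the article gives none of these: SDQ-Emotional SD 2.0, slope of T3 on baseline 0.6 (also the correlation), 120 treated children per band, and a gap of 1 point at both T1 and T3. Clustering by family is ignored. The true difference in effect between bands is zero.

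- Change from T1: expected contrast = 1.0 − 1.0 = 0, rejected about 5% of the time.
- T3 adjusted for baseline: contrast = gap × (1 − slope) = 1.0 × 0.4 = 0.40. SE = 2.0 × √(1 − 0.36) × √(2/120) = 0.207. Ratio 1.94, two-sided rejection about 49%. Gaps of 0.5 and 1.5 points give contrasts of 0.20 and 0.60, with rejection about 16% and 83%.
- T3 unadjusted: contrast = 1.0, the whole gap. SE = 2.0 × √(2/120) = 0.258. Ratio 3.87, rejection about 97%.

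For scale, the planned effect for H1 in the sample size section (1.1) is 0.40.

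**Shift that arises between T1 and T3.** This is a separate case, such as natural change that differs by age. A simulation of 1,000 runs per setting assumed 700 children over both arms, two age groups, SD 2.3, baseline correlation 0.5 and the same effect of −0.40 at every age, again without clustering. The within-arm contrast was adjusted for baseline.

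| Shift (points) | Within-arm contrast significant | Arm-by-age interaction significant |
|---|---|---|
| 0 | 5% | 5% |
| 0.2 | 15% | 5% |
| 0.4 | 44% | 5% |
| 0.8 | 95% | 5% |

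The within-arm estimate was close to the full shift each time; the mean interaction estimate was about zero. These figures do not confirm the 49% above, which concerns a gap already present at baseline.

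**Module slope.** With 350 treated children, no true effect, and an unmeasured engagement trait that both raises module use and lowers the score by 0, 0.2 or 0.4 points per SD of the trait, the module slope was significant in 5%, 30% and 80% of runs.

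**Power of the replacement.** Take the first set of assumptions with 120 children in each of four cells (two bands, two arms). The interaction SE = 2.0 × 0.8 × √(4/120) = 0.292. If the effect differed between the bands by 0.40, the ratio would be 1.37 and power about 28%.

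**The case against.** The strongest reply is that nothing in the article misuses these analyses. They are follow-up analyses, none of H1–H15 concerns age or modules, and the wording is about differences in outcomes, not in effect. The stated objective is an overall effect in ages 3 to 17. All of that stands. A reader might infer that the trial is obliged to estimate effect by age, or that the authors intend to claim differential benefit or a dose-response. The article says neither.

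A second reply is that the distortion may be nil. The sentence begins with change over time, and a stable gap, including most of a stable reporter difference, cancels in change scores. Baseline score is listed only as a potential covariate of the main models, and the follow-up model is left open. This also stands, so the 49% must not be read as a property of the plan. It does not rescue the age comparison: change scores leave natural change that differs by age, and no within-arm model can remove that.

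Third, controls do not resolve everything. Reporter is fixed by age and is constant in the 3–5, 6–8 and 13–17 bands. Controls remove differences in level and trend, but cannot show whether an effect that varies does so by age or by reporter, except within 9–12.

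Fourth, module count does not exist in the control arm, and children choose what is relevant to them. A low share of the available modules is therefore not low adherence by design, and scaling by modules available is debatable. A complier estimate with arm as instrument answers a different question and needs an exclusion assumption. Tickets tied to modules in one arm only make that assumption harder to accept. Neither should be required.

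**Conclusion.** The point holds for the age comparison as a flaw in what that analysis can show. It discards the controls although age is known in both arms, so it cannot distinguish a difference in effect from differences in level, trend or reporter. Its numerical size is not fixed by the article: for a stable gap it runs from nothing (change scores) through about 40% of the gap (baseline adjustment, assumed slope 0.6) to the whole gap (unadjusted). A gap that opens after baseline comes through almost in full. The gaps, SDs, slope or correlation and group sizes are all assumptions.

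For modules, the within-arm analysis is acceptable only as a description, and raw count is entangled with age because the bands offer 4, 8, 10 and 10 modules.

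It would be tempting to conclude that the trial's effectiveness claims are compromised. The documents do not support that: the tests of H1–H15 compare the randomised arms and are untouched.

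**What to change.** In the Statistical analyses section:

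1. Replace the within-arm age comparison with an arm-by-age-group interaction in all randomised children. Place controls in the same four bands by age at baseline. Adjust for baseline score and reporter, and keep the planned allowance for clustering by family.
2. Report the effect in each band with its interval, labelled exploratory. State that effect modification by age and by reporter cannot be separated outside the 9–12 band.
3. Label the module analysis as descriptive and non-causal, and adjust it for age group or stratify it by age group. A complier estimate is optional; if given, state its exclusion assumption.

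The cost is a few sentences. Age, reporter, arm and module use are already part of the planned data. The downside is low power for the interaction (about 28% in the illustration above), so the intervals will be wide and a non-significant interaction must not be read as evidence of equal effect.

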
Digital interventions are often more affordable, easier to scale, and have the ability to be updated and expanded (Kazdin and Blase, 2011). Digital interventions may also be preferred by people experiencing relationship dissolution, as they can be more convenient, accessible anytime anywhere, and help reduce stigmatization (Bowers et al., 2011; Greenberg et al., 2019). Recent research shows that digital interventions for distressed couples and adults undergoing relationship dissolution and divorce yield moderate to large effects (Doss et al., 2016; Hald et al., 2020a). However, there is a dearth of research-based digital interventions aimed at youths (Bowers et al., 2014; Haine et al., 2003). To our knowledge, there is only one digital intervention aimed directly at youths of divorced parents, namely the Children of Divorce-Coping with Divorce (CoD-CoD) (Boring et al., 2015), with another under development (O'Hara et al., 2023). The CoD-CoD intervention consists of five self-paced modules, adapted from evidence-based cognitive–behavioral coping programs for adolescents (aged 11–16 years) (Boring et al., 2015). Evaluations of the CoD-CoD interventions showed that the intervention was successful in reducing youth-reported mental health problems and adjustment problems among youths experiencing parental relationship dissolution and also among youths experiencing high levels of parental conflict (Boring et al., 2015; O'Hara et al., 2022). Although the CoD-CoD has demonstrated promising results, the CoD-CoD has only been developed for and tested among older youths. The intervention currently under development (O'Hara et al., 2023) tests 3 digital modules focused on teaching coping skills (i.e., reappraisal, distraction, and relaxation) to help children cope with a high-conflict parental divorce. However, similar to CoD-CoD, the intervention only targets a small subset of children, specifically those aged 9 to 12. As relationship dissolution affects youths across different ages (Pedro-Carroll, 2005), it is imperative to develop interventions that can encompass and be scaled to multiple age groups.

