Families are randomized to either the intervention or the wait-list control group. Randomization is performed electronically, with a random number generator, and randomization occurs at the family level, such that parents and children are randomized to the same group, at a 1:1 allocation ratio. Participants (i.e., parents and children aged 11–17) are sent e-mails and/or text messages containing links to the online T1 survey, and upon completion of the T1 survey, they are informed of their group allocation. Intervention group participants receive access to the intervention immediately. Access to SES NXT is provided to the specific child, for whom the T1 survey is completed; that is, if a mother completes a survey for “Child 1”, but not “Child 2”, then only “Child 1” receives access to SES NXT. User accounts are automatically generated for each child that is signed up.

After signing up, parents receive an e-mail and/or text message with a link to a short survey about themselves. Parents also receive individual links via e-mail and/or text message to questionnaires for each child aged 3–10 years. Youths aged 11–17 years receive links via e-mail and/or text message to surveys for them to complete on their own; in cases, where children do not have their own e-mail address or mobile phone number, parents may list theirs and share the survey with the youth. Upon completion of the baseline (T1) questionnaire, participants receive follow-up questionnaires 4 weeks (T2) and 12 weeks post-baseline (T3). Even if participants do not complete the T2 survey they still receive the T3 survey. Table 1 provides an overview of the scales completed at each timepoint. Participants in the control group receive access to SES NXT after T3, regardless of whether they respond to the T2 and T3 surveys.

**Table 1 t0005:** Overview of measurement.

	Parent	Age 3	Age 4–10	Age 11–17
	Self-report	Parent report	Parent report	Self-report
Socio-demographic questions and relationship/divorce questions	T1			
Divorce conflict (Hald et al., 2020b)	T1, T2, T3			
Depression symptoms (PHQ-2; Kroenke et al., 2003)	T1, T2, T3			
Anxiety symptoms (GAD-2; Kroenke et al., 2007)	T1, T2, T3			
Strength and Difficulties Questionnaire (Goodman et al., 1998)		T1, T2, T3	T1, T2, T3	T1, T2, T3
Physical health: Somatization (SDQ, item 3), body dissatisfaction, sleep quality		T1, T2, T3	T1, T2, T3	T1, T2, T3
School and daycare attendance (Heyne et al., 2020)		T1, T2, T3	T1, T2, T3	T1, T2, T3

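### The follow-up analysis by age version uses the intervention arm alone, so it mixes natural age and rater differences with any difference in treatment effect

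*Protocol article*

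**What the plan says.** Section 1.6 (Statistical analyses) ends with additional follow-up analyses. One compares the arms over time, looking for "differential change over time for the two groups, as reflected in a time-by-group interaction effect". The others are, "for the intervention group, to examine differences in the outcomes based on intervention age group", and, under the same restriction, by how many modules were completed. The age-version comparison is therefore fixed to the intervention arm. Age otherwise appears only among the potential main-effect covariates of the main models, next to the baseline score.

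Three other statements bear on this:
- Section 1.4 (Intervention description): "The intervention has four age categories", namely 3–5, 6–8, 9–12 and 13–17 years.
- Section 1.5 (Measures): "parents complete questionnaires on behalf of their children aged 3–10, while youth aged 11–17 complete the questionnaires themselves".
- Section 1.3 (Procedure): "randomization occurs at the family level, such that parents and children are randomized to the same group, at a 1:1 allocation ratio".

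**The concern.** A comparison of outcomes between age versions among treated children has no comparator. If SDQ scores differ by age, or differ because a parent answers for one child and another child answers for itself, the versions will differ even when the programme does nothing or works equally well at every age. Age version and rater are almost fully tied together: 3–5 and 6–8 are wholly parent-rated, 13–17 is wholly self-rated, and 9–12 is mixed.

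The comparator exists. Control children cover the same ages and raters, their ages are collected at sign-up, and they complete the SDQ at all three time points (Table 1). The version each would have received is therefore known. Number of modules completed has no counterpart in controls before T3, which may be why the sentence is limited to one arm, but age group has no such limit.

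At stake is how a stated analysis can be read. The introduction argues that "it is imperative to develop interventions that can encompass and be scaled to multiple age groups", and the objective covers ages 3 to 17, so readers will naturally take a reported age-version difference as a difference in effect. Section 1.6 applies the 0.05 threshold to all analyses.

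**Working it through.** **The plan's own figure.** The roughly 700 clusters in section 1.1 rest on a difference of 0.40, 90% power and alpha 0.05. SD, children per family and ICC are not given, so the figure cannot be reproduced exactly. With one child per family and a two-sided test, total n = 4(1.96 + 1.28)² SD² / 0.40². SD 1.63 gives 698. With 1.5 children per family the implied SD is about 1.8–2.0, and with 2 children about 1.9–2.3 (ICC 0 to 0.5). An SD of 2 is thus compatible with the plan. The point does not depend on the 700.

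**What each contrast estimates.** Let μ be the natural T3 level in a band (age and rater together), τ the treatment effect, δ any natural change from T1 to T3, and ρ the T1–T3 correlation (equal SDs). For band k against band j:
- within-arm, unadjusted: (μk − μj) + (τk − τj)
- within-arm, baseline-adjusted, with μ the stable level: (1 − ρ)(μk − μj) + (δk − δj) + (τk − τj)
- band-by-arm interaction: τk − τj, because the controls carry the same μ and δ.

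**Simulation 1.** Assumptions: 700 families, about 1.5 children each, SD 2, ICC 0.3, ρ = 0.6, 70% T3 response, no effect in any band, 400 trials per scenario, family-clustered standard errors. Rejection rates at 0.05:

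| Natural level by band | Within-arm, unadjusted | Within-arm, adjusted | Interaction |
|---|---|---|---|
| 0, 0, 0.25, 0.5 | 38% | 12% | 5.2% |
| 0, 0.2, 0.4, 0.8 | 68% | 23% | 4.8% |
| 0, 0.3, 0.6, 1.0 | 86% | 30% | 4.8% |
| all equal | 3% | 5% | 6% |

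A repeat under the same assumptions gave 36–84% unadjusted and 13–29% adjusted.

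**Simulation 2.** Assumptions: 700 children 1:1, four equal bands, no clustering, SD 2, ρ = 0.6, natural levels 0, 0.2, 0.5, 1.0, 1000 trials per scenario. Each cell gives the rejection rate and the mean estimate for oldest minus youngest:

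| Scenario | Within-arm, unadjusted | Within-arm, adjusted | Interaction |
|---|---|---|---|
| no effect | 84%; 0.99 | 27%; 0.39 | 4.6%; −0.01 |
| uniform effect −0.40 | 82%; 0.98 | 26%; 0.38 | 4.5%; −0.02 |
| no effect, natural change 0, 0, 0.1, 0.3 | 99%; 1.32 | 74%; 0.71 | 4.2%; 0.02 |
| effect 0, −0.2, −0.5, −1.0 | 4.5%; 0.00 | 55%; −0.59 | 75%; −1.00 |

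The estimates follow the formulas. Adjusted with no effect: (1 − 0.6) × 1.0 = 0.40. With natural change: 0.40 + 0.30 = 0.70. With a true difference of −1.0: 1.0 − 1.0 = 0 unadjusted, 0.40 − 1.0 = −0.60 adjusted, and −1.0 for the interaction.

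**Power of the alternative.** Under the assumptions of simulation 1, with the planned 0.40 confined to the two older bands, the interaction test rejects in about 26–27% of trials.

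**The case against.** This is one clause among follow-up analyses. None of H1–H15 concerns age version, and the primary comparisons are randomised. That stands and limits the weight of the point.

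The article does not say the age-version comparison is unadjusted. It neither fixes nor excludes baseline adjustment there, so the 36–86% belongs to the least favourable reading. That also stands, and the adjusted 12–30% is the fairer headline. It is still well above 5%.

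No age or rater shift is given in the document, and with no shift the within-arm test behaves correctly. The figures show a mechanism and do not measure this trial. The lack of separation in the formulas does not depend on them.

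Stronger readings are tempting and should be resisted:
- A reader might infer that the contrast measures only natural differences. It measures these mixed with any true difference in effect.
- A reader might infer that real differences would be missed. The unadjusted 4.5% in the last scenario arises because the age shift and the benefit were set to cancel. The adjusted test rejects in 55% there, though with a biased estimate.
- A reader might infer that the trial cannot tell which versions to roll out. The article ties no such decision to this analysis, and both arms' data are collected.
- A reader might treat the versions as four separate programmes. Section 1.4 describes one intervention whose content is largely shared across ages.

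**Conclusion.** The point holds for the analysis as stated: a within-arm comparison by age version cannot show whether the treatment effect differs between versions. Under assumed shifts of 0.5 to 1.0 points and no effect, it gives a false signal in about 12–30% of trials with baseline adjustment and about 36–86% without, against about 5% for the interaction. The shifts, SD 2, ICC 0.3, correlation 0.6 and 70% response are assumptions, and natural change over time that differs by age would raise the adjusted rates further. H1–H3 are unaffected. It is worth correcting because the article fixes the wrong population for this question and the right one is already in the data.

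**What to change.** Split the sentence in section 1.6 into two analyses.

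1. Age version, in both arms: add age band (3–5, 6–8, 9–12, 13–17, from age at sign-up), allocated group and their interaction to the baseline-adjusted primary GEE. Report the intervention-minus-control difference at T3 with 95% CI in each band and one 3-df interaction test, labelled exploratory.
2. Modules completed: keep as a separate statement, still restricted to the intervention group. Simply deleting the restriction from the present sentence would remove it here too, where it is needed.

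The cost is three band terms and three interaction terms, with no new data. The multiple imputation should carry the same interaction. With four equal bands, each band's interval is roughly twice as wide as the overall one (√4 = 2), and interaction power is only about a quarter in the case worked above, so a non-significant test must not be read as equal effects. Because rater follows age, the interaction also cannot say whether a difference in effect comes from the version or from who reports.
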